#### 2.4.3. Intervention Phase

##### Functional Remediation

All study participants will continue receiving their usual treatment, and their service use will be documented. In addition, the intervention arm will receive FR, a manualized, group-based neurocognitive behavioral training program based on ecological tasks adapted to real-world situations [57]. The program is strongly focused on the development of cognitive strategies and their transfer to everyday situations, involving modeling techniques, role-playing tasks, self-instruction, positive reinforcement and metacognitive cues. These elements will be combined with psychoeducation sessions and with homework material assigned and discussed during each training session.

The program consists of 21 90-minute weekly sessions, in which a trained therapist and co-therapist work with 10–12 patients. The first 3 sessions cover psychoeducation on neurocognitive deficits, followed by 13 sessions of neurocognitive training sequentially targeting different cognitive domains (attention, memory and executive functions) and comprising paper-and-pencil cognitive exercises carried out either individually, in pairs or in small groups. Lastly, 5 sessions are dedicated to aspects of skills training, such as autonomy, communication, interpersonal relationships and stress management. Treatment will be administered by mental health professionals technically experienced in clinical neuropsychology, leading group therapies and BD care, identifying psychologists as main therapists and other professionals as co-therapists. One psychologist ([name]) received direct specific training in the delivery of FR by the team of Barcelona Bipolar Disorders and Depressive Unit, Institute of Neurosciences, University of Barcelona, IDIBAPS, CIBERSAM, Hospital Clínic of Barcelona, who developed the program. Staff training will be conducted by [name] before study start. Therapists and treatment teams will not take part in screening and outcome evaluations and will not disclose the treatment condition.

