### 2.2. Trial Design and Setting

This is a pilot randomized and rater-blind controlled trial involving 54 clinically stable subjects with a diagnosis of BD type I or II and comprising a 6-month intervention phase and a 6-month follow-up period. Study participants will be assigned to either FR in addition to TAU (n = 27) or TAU alone (n = 27). Clinical assessments will be conducted at baseline, post-treatment and after a follow-up of 6 months (shown in Figure 1).

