#### 2.4.2. Allocation and Blinding

Patients fulfilling all inclusion criteria will be randomized to the two parallel groups by a researcher not involved in the subsequent trial procedures, using a computer-based system (1:1 ratio). The allocation sequence will not be based on any stratification procedure, and all the details related to randomization will be kept locked following treatment allocation (Figure 1).

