## 3. Measurement

### Statistical Analyses

All the analyses will be carried out using SPSS version 14.0 for Windows (SPSS Inc., Chicago, IL, USA, 2005).

Improvements in psychosocial functioning and cognitive performance will be assessed using effect size estimates obtained from within- and between-group differences at repeated measures analyses of variance (rm-ANOVAs). In case of attrition rate > 20%, a mixed model will be employed, under the missing at random (MAR) assumption. Regarding clinical symptoms, treatment effects will be compared among patients with and without residual symptoms (≥1 on Y-MRS, ≥3 on HAM-D) using t-tests.

Given the small sample size, the investigation of potential predictors of response through regression analyses should be considered largely explanatory. However, some regression analyses will be performed as deemed important in light of the feasibility nature of this trial; variables of interest will include participants’ age, duration of illness, baseline functioning, baseline cognitive performance and change in cognitive performance as well as potentially emerging predictors of dropout. In fact, participants leaving the study early will be compared with those completing all study procedures in terms of demographic and clinical variables using inferential statistics to assess potential moderators.

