#### Power—Sample Size Calculation

The required sample size was estimated based on power calculations performed on the software G*Power [65] and assuming an effect size of 0.25 on the ANOVA group × time interaction for the primary outcome (psychosocial functioning measured with the FAST scale). This effect size is in line with that observed in previous studies adopting similar procedures and intervention paradigm [39]. With alpha at 0.05, the effect size could be detected with 95% power when enrolling a sample of 44 participants (22 per group). Assuming 20% attrition, it was decided to set the recruitment target at 54 participants (27 per group).

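### FR is given in groups, so its arm rests on about two or three therapy groups, but the analysis and sample size treat patients as independent; any positive within-group correlation understates the standard error

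*Protocol article*

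**What the plan says.** All places are in the protocol article.

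- **Delivery (2.4.3, Functional Remediation).** FR is "a manualized, group-based neurocognitive behavioral training program" of 21 weekly sessions, "in which a trained therapist and co-therapist work with 10–12 patients". It uses role-play and exercises done in pairs or small groups.
- **Comparator (2.5, Treatment as Usual).** TAU patients receive medication under guidelines and no FR. No therapy group is described for them.
- **Allocation (2.2 and 2.4.2).** Participants are "assigned to either FR in addition to TAU (n = 27) or TAU alone (n = 27"), and "The allocation sequence will not be based on any stratification procedure".
- **Analysis (3, Statistical Analyses).** Effects come from "repeated measures analyses of variance (rm-ANOVAs"). A mixed model replaces this only if attrition exceeds 20%, and its stated purpose is missing data. No term for therapy group or therapist is named in either model.
- **Sample size (Power—Sample Size Calculation).** The calculation is made "assuming an effect size of 0.25 on the ANOVA" group × time interaction, with alpha 0.05. It concludes that "the effect size could be detected with 95% power" with 44 participants, 22 per group, and raises this to 54 for attrition. No ICC or design effect is mentioned.
- **Limitations (4, Discussion).** The small sample is discussed; the number of therapy groups is not.

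**The concern.** This is a partially nested design. FR patients share a therapist pair, peers and 21 sessions. TAU patients share none of that. If one FR group does better or worse than another for reasons of leadership or group dynamics, its members' outcomes move together, and 27 such patients carry less information than 27 independent ones. An rm-ANOVA without a group term does not count that extra variance. The standard error would then be too small, the p-value too low and any interval built on it too narrow. One unusually good group could also pass for an effect of FR.

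This is not a detail that can be assumed to sit in an analysis plan. The article itself fixes both the analysis model and the power model, and both treat patients as independent.

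**Working it through.** **Inputs from the article.** f = 0.25; alpha = 0.05; N = 44 (22 per arm); 27 per arm recruited; 10–12 patients per FR group; three assessments (T0, T1, T2).

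**Assumptions, because the article does not give them.** Correlation between visits ρ = 0.5; sphericity; ICC = 0.02, 0.05 or 0.10.

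**1. Reproduce the stated sample size.** For the interaction with k = 2 arms and m_v = 3 visits:

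λ = N·f²·m_v/(1−ρ) = 44 × 0.0625 × 3 / 0.5 = 16.5, with df = (k−1)(m_v−1) = 2 and (N−k)(m_v−1) = 84.

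Power is 0.956. At N = 42, λ = 15.75 and power is 0.946, so 44 is the smallest even N that reaches 95%. The figure is recovered as a calculation on independent patients with no design effect. This depends on ρ: with three visits and ρ = 0.3 or 0.7 the required N would be 60 or 28.

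**2. Number of FR groups.** 27/12 = 2.25 and 27/10 = 2.7; for 22 completers, 22/12 = 1.83 and 22/10 = 2.2. The arm therefore rests on about two or three groups.

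**3. Design effect and standard error.** With FR groups of size m, the FR-arm variance is multiplied by DE = 1 + (m−1)·ICC and the TAU variance is unchanged. With equal arms, the variance of the difference is multiplied by (1+DE)/2. For two groups of 11, λ is divided by that factor:

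| ICC | DE | (1+DE)/2 | True SE / unadjusted SE | λ | Power at N = 44 |
|---|---|---|---|---|---|
| 0 | 1.0 | 1.00 | 1.00 | 16.5 | 0.956 |
| 0.02 | 1.2 | 1.10 | 1.05 | 15.0 | 0.936 |
| 0.05 | 1.5 | 1.25 | 1.12 | 13.2 | 0.902 |
| 0.10 | 2.0 | 1.50 | 1.22 | 11.0 | 0.839 |

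These powers are approximate: they take the ICC as known and keep the test at its nominal level. With the same 22 patients in three groups they are 0.944, 0.923 and 0.886. If all 54 patients were retained, in three FR groups of 9, they would be 0.976, 0.961 and 0.929.

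**4. Type I error of the unadjusted rm-ANOVA.** This was simulated with 20,000 trials per setting, a nominal 5% level, and a shared FR-group effect at T1 and T2:

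| ICC | Two groups of 11 | Three groups of 9 |
|---|---|---|
| 0 | 5.2% | 5.0% |
| 0.02 | 5.9% | 6.0% |
| 0.05 | 7.9% | 7.3% |
| 0.10 | 11.2% | 10.0% |

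A t-test that ignores clustering gave nearly the same: 6.0, 8.0 and 11.4% for two groups, and 6.0, 7.2 and 9.8% for three.

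**5. Could the groups be modelled directly?** A small-sample analysis of FR group means of T1 change, at ICC 0.05 and a step effect equivalent to f = 0.25, had power of about 0.60 (22 patients, two groups) to 0.78 (27 patients, three groups). Its type I error was still about 0.08 and 0.06. Two or three groups do not support a reliable estimate of the group variance.

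**6. Group size against arm size.** Two groups hold at most 2 × 12 = 24; three need at least 3 × 10 = 30. The arm of 27 lies between.

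**The case against.** The strongest objection is that the inflation is conditional. A reader might infer that this trial's type I error is inflated as a matter of fact. The article does not support that: it gives no ICC, at zero there is no inflation, and at 0.02 the error rate is only about 6%. FR is manualised and staff are trained centrally, which may keep differences between groups small. The number of therapist pairs is not stated, so their contribution is unknown. The analysis section also speaks of effect size estimates and does not name confidence intervals, although the same standard error underlies both. This objection stands, and it is why the result is given as a range.

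The article also calls the trial a pilot, with a feasibility and exploratory character. That softens the consequence but does not remove it, because the article states an efficacy hypothesis and claims 95% power for it.

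A reader might also take TAU patients to be free of all clustering. They come from three operative units and receive individual case management, so both arms may be nested within units. Only therapy-group clustering is peculiar to FR.

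Nor does the article show that an FR arm of 27 is impossible. The range of 10–12 can be read as describing the manualised programme, no number of groups is fixed for this trial, and 22 completers would make two groups of 11, though those groups would have to start above 12. What remains is a mismatch of wording that needs clearing up.

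**Conclusion.** The point holds in conditional form. FR is group-delivered, TAU is not, and both the analysis and the sample size assume independent patients. For any positive ICC the direction is certain: the standard error is understated and the stated 95% power is too high at the planned N = 44. The size depends on an ICC that has to be assumed. It is small at 0.02 and material from about 0.05, where type I error is about 7–8% and power at N = 44 is about 90% with two groups of 11. The power figures also assume three visits and ρ = 0.5, and they would be better if attrition were below the planned 20%.

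Two demands that might seem to follow do not. A random group effect alone would not repair the analysis with so few groups, and nothing in the article justifies making an efficacy claim depend on one particular ICC. The mismatch between group size and arm size is a separate, minor point.

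**What to change.** 1. Record each FR patient's therapy group during delivery.
2. Keep the primary analysis and pre-specify beside it a sensitivity analysis that inflates the FR-arm variance by 1 + (m−1)·ICC at fixed ICCs of 0.02, 0.05 and 0.10. Fixed values are used because two or three groups cannot estimate the ICC reliably.
3. Restate power over the same ICCs in place of the single 95%, and state the assumed number of visits and between-visit correlation.
4. Add the small number of therapy groups to the limitations, as a restriction on efficacy conclusions.
5. Reconcile the group size in Functional Remediation with the arm size in Trial Design and Setting.

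The cost is one extra recorded variable, a short addition to the analysis, and some wording. No extra patients or visits are needed. The downside is wider intervals in the sensitivity analysis and a lower stated power.

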### 2.5. Treatment as Usual

Subjects enrolled in the TAU group will receive the prescribed pharmacological treatment according to the guidelines and good clinical practices envisaged for BD [50]. Participants recruited to the TAU group will not receive FR intervention.

Subjects enrolled and belonging to both groups will have access to other evidence-based treatments for bipolar disorder, according to clinical decisions.

### 2.6. Assessment Phase

Outcomes will be evaluated at baseline (T0), at the end of active treatment phase (T1) and 6 months thereafter (T2), using standardized and previously validated rating instruments based on Italian normative data. Assessments will be conducted by two trained residents in psychiatry, with at least 1 year of experience, not involved in treatment delivery for this trial and blinded to study treatment condition. Inter-rater reliability will be verified before study start. Patients will be instructed not to reveal information on their therapy during assessments. Eventual cases of blinding violations will be reported. Effectiveness of blinding will be verified at the end of the trial, asking assessors to guess which group the patients belong to and then verifying the answers using the McNemar test of independence [58]. Assessment at T1 is meant to obtain effectiveness data, together with essential information on trial and intervention feasibility. A follow-up observation will be performed to verify the long-term persistence of effects and their translation to everyday functioning, which is hypothesized to consolidate over time [59,60] (Figure 2).

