### 2.7. Outcome Measures

The primary outcome for this study is the efficacy of FR in improving psychosocial functioning, measured using the FAST [56]. This is a simple rater-administered instrument specifically developed for patients with BD and comprising 24 items on various aspects of everyday functioning among those more frequently impaired. The FAST global score (0–72) reflects the patient’s level of disability. This scale has been consistently used in FR trials and already proven to be sensitive to effects of this treatment [39].

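### The McNemar check of rater blinding ignores how many guesses are correct: it is insensitive to unblinding that is similar in both arms, and a rejection is not specific to unblinding

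*Protocol article*

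**What the plan says.** Protocol article, section 2.6 (Assessment Phase): outcomes are rated by two psychiatry residents who are "not involved in treatment delivery for this trial and blinded to study treatment condition". On the check itself the section states: "Effectiveness of blinding will be verified at the end of the trial". The procedure is "asking assessors to guess which group the patients belong to and then verifying the answers using the McNemar test of independence", with a literature citation. The section names no other blinding statistic and gives no significance level for this test and no rule for reading the result. It also says that patients will be told not to disclose their therapy and that violations of the blind will be reported.

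Section 2.2 gives the allocation: 27 patients to FR plus TAU and 27 to TAU alone. Section 2.7 describes the primary outcome, FAST: "This is a simple rater-administered instrument specifically developed for patients with BD".

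**The concern.** McNemar's test asks whether two paired binary variables have the same marginal frequency. Independence is a different hypothesis. With guess paired to true arm, the test asks only whether assessors said FR about as often as FR was allocated. Whether they said it of the right patients does not enter the statistic.

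The blind matters here because FAST is rater-administered, the control arm has no group programme matching the 21 FR sessions (sections 2.4.3 and 2.5), and patients know whether they attend. Rater blinding is thus the main protection of the primary comparison against detection bias. Reporting of violations captures recognised disclosures. The guess exercise is the planned means of finding unblinding that nobody noticed, and the named test does not measure it.

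**Working it through.** **The plan's own figures.** The article gives no number for the blinding check. Its one design calculation, which is not in dispute, supplies the evaluable arm size of 22. For f = 0.25, alpha 0.05, N = 44, two groups and m = 3 time points, with correlation 0.5 and sphericity assumed because neither is stated:

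- λ = f²·N·m/(1 − ρ) = 0.0625 × 44 × 3 / 0.5 = 16.5, on 2 and 84 degrees of freedom.
- Power is 95.6%; at N = 42 it is 94.6%. The stated 44 for 95% power is reproduced.

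**Inputs.** 27 per arm (section 2.2), or 22 per arm evaluable (sample-size section). Assumed: one FR/TAU guess per patient, paired with true allocation, and a two-sided 0.05 level where rejection rates are quoted.

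**Formulas.** Let b = FR patients guessed as TAU and c = TAU patients guessed as FR.

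- Exact McNemar: two-sided p from Binomial(b + c, 0.5), with p = 1 when b + c = 0. The uncorrected chi-square form (b − c)²/(b + c) is then 0/0. Correct guesses appear nowhere.
- Comparator: Fisher's exact test on the 2×2 table of true arm by guessed arm.

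**Results, 27 per arm.**

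| Guessing pattern | FR correct | TAU correct | b | c | McNemar p | Fisher p |
|---|---|---|---|---|---|---|
| All correct | 27 | 27 | 0 | 0 | 1.0 | 1.0e-15 |
| 24/27 correct in each arm | 24 | 24 | 3 | 3 | 1.0 | 8.9e-9 |
| 22/27 correct in each arm | 22 | 22 | 5 | 5 | 1.0 | 7.0e-6 |
| Chance-level split | 13 | 14 | 14 | 13 | 1.0 | 1.0 |
| Unequal accuracy | 25 | 20 | 2 | 7 | 0.18 | 8e-7 |
| One-sided: all FR identified, TAU at chance | 27 | 13 | 0 | 14 | 0.0001 | 3.6e-5 |
| No information: FR guessed for everyone | 27 | 0 | 0 | 27 | 1.5e-8 | 1.0 |
| No information: FR guessed for 20/27 in each arm | 20 | 7 | 7 | 20 | 0.019 | 1.0 |

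Checks by hand: for FR guessed for everyone, 2 × 0.5^27 = 1.5e-8, and by symmetry the same for TAU guessed for everyone. For the one-sided row, 2 × 0.5^14 = 0.00012. For unequal accuracy, 2 × (1 + 9 + 36)/2^9 = 92/512 = 0.18. Bang's index at 22/27 correct is 2 × 22/27 − 1 = 0.63 in each arm.

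**Probability of rejection at 0.05** (exact enumeration, 27 per arm):

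| Scenario | McNemar | Fisher |
|---|---|---|
| 50% correct in both arms | 0.3% | 2% |
| 70% correct in both arms | 0.9% | 76% |
| 80% correct in both arms | 1.2% | 99% |
| 100% correct in both arms | 0% | 100% |
| 90% of FR and 60% of TAU correct | 52% | 97% |
| 100% of FR and 50% of TAU correct | 99.9% | 99.9% |
| No information, FR guessed 80% of the time | 95% | 2% |

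With 22 per arm and 80% correct in both arms the rates are 1.0% for McNemar and 98% for Fisher, so attrition does not change the picture.

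**The case against.** Four arguments limit the point.

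**The test is not blind to all unblinding.** A reader might infer from p = 1 under perfect guessing that McNemar can never detect a broken blind. That goes too far. If all 27 FR patients are identified and TAU is guessed at chance, it rejects (p = 0.0001). One-sided leakage is plausible, since only FR patients have group sessions to mention. This stands. But the rejection comes from the surplus of FR guesses, and the same surplus without any information also rejects.

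**No decision rule is written.** A reader might also infer that the plan would declare the blind intact after a non-significant result. The article states no threshold and no consequence. Misreading is a reasonable fear, but it is not something the plan commits to.

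**The table is not defined.** The authors may intend a guess-by-arm association test under the wrong name; the phrase about independence hints at it, and the cited source is not at hand. Guess against allocation remains the reading that fits checking the answers. If only the name is wrong, it still has to be corrected, because an analyst following the text would run McNemar.

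**The check is ancillary and recoverable.** It does not enter the FAST analysis, the effect estimate or the sample size. The guesses already planned yield the guess-by-arm table, so a suitable statistic can be computed later from the same data. Other safeguards exist: assessors are separate from treatment delivery, therapists are not to disclose the condition (section 2.4.3), and violations are reported. All of this stands and limits the severity.

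On timing, a single guess at trial end cannot describe the blind at T1 six months earlier. Yet a guess at T1 may prime the same two assessors for T2, and it too would be coloured by perceived outcome. The article's choice of timing is a trade-off and not an error.

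**Conclusion.** The point holds as a fault in a stated method. McNemar is misnamed as a test of independence and does not suit the question. When accuracy is similar in both arms, it returns p at or near 1 whether the guesses are perfect, clearly better than chance, or at chance; at 80% accuracy it rejects about 1% of the time, against 99% for Fisher. When it does reject, the cause may be unblinding or merely a habit of guessing one arm.

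The conclusion assumes one guess per patient paired with true allocation. The p = 1 results do not depend on the significance level; the rejection rates assume 0.05.

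Severity: should be fixed. What is at risk is the credibility of the blinding report for a rater-administered primary outcome.

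**What to change.** In section 2.6, replace the McNemar test with Fisher's exact test of association between guessed and true allocation, a blinding index per arm (for example Bang's) with 95% confidence interval, or both. State that the table is guess by true allocation, and report the number of correct guesses in each arm.

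The cost is one sentence; the guesses already planned suffice. Also recording a guess after the T1 rating is optional: it would describe the blind at that visit, at the risk of priming the same assessors for T2. If it is wanted, it has to be decided before the T1 ratings, because those guesses cannot be recovered afterwards.

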### 2.7. Outcome Measures

The primary outcome for this study is the efficacy of FR in improving psychosocial functioning, measured using the FAST [56]. This is a simple rater-administered instrument specifically developed for patients with BD and comprising 24 items on various aspects of everyday functioning among those more frequently impaired. The FAST global score (0–72) reflects the patient’s level of disability. This scale has been consistently used in FR trials and already proven to be sensitive to effects of this treatment [39].

Additional outcomes will be *evaluated as secondary endpoints:* (a) global neurocognitive performance measured with the Brief Assessment of Cognition in Affective Disorders (BAC-A), Italian version [61]. This scale has been derived from a neuropsychological battery commonly used to assess cognitive performance in people living with schizophrenia, the Brief Assessment of Cognition in Schizophrenia (BACS) [62], but is designed to be sensitive and specific in patients with affective disorders such as BD. It contains six tests that assess different cognitive domains (List Learning for Verbal Memory, Digit Sequencing Task for Working Memory, Token Motor Task for Motor Speed, Verbal Fluency Category Instances for Semantic Fluency and Controlled Oral Word Association Test for Letter Fluency, the Tower of London Test for Executive Functions and Symbol Coding for Attention and Motor Speed) that are contained in the BACS and features also an affective processing test [63]. The six core BACS measures can be standardized into z-scores according to available normative data [61], and a global cognition composite score can be calculated by averaging the scores of single scales. (b) Socio-cognitive performance measured with the Mayer–Salovey–Caruso Emotional Intelligence Test (MSCEIT), Italian version [63]: this test assesses emotional processing ability and includes a total of 141 items divided in 8 tasks. The score on these tasks can be combined into 4 sub-scales that can be further combined in 2 areas and with a total score measuring global emotional intelligence. (c) Manic symptoms severity measured with the Y-MRS [54], a scale composed of 11 items. Four core items are graded from 0 to 8 without odd scores, and seven items are graded from 0 to 4; each item has specific anchor points, and higher scores reflect more severe manic symptoms. (d) Depressive symptoms severity measured with the HAM-D [55], a scale composed of 17 items. Each item has specific anchor points; 8 items can be graded from 0 to 2 and 9 items can be graded from 0 to 4, with higher scores reflecting greater symptoms severity; a score ≤ 7 corresponds to the absence of depressive symptoms.

The number and patterns of dropouts will also be reported, along with descriptions of the rate of enrollment and consent of eligible subjects, the percentage of session attendance and the reasons for non-attendance.

Patients will be considered dropouts in the following cases: (a) withdrawal of consent; (b) emergence of a full-blown mood episode and/or major change in drug therapy needed in order to prevent this eventuality within the study period; (c) discontinuation of drug therapy for ≥5 consecutive days; (d) missing ≥5 consecutive FR sessions.

Additional information will be collected regarding demographic and clinical characteristics of the included participants: age, sex, employment status, familiarity for psychiatric disorders, BD type I/II, cycling, seasonality, age at onset, duration of illness, number of previous episodes, history of psychosis, history of suicide attempts, presence of baseline residual symptoms and baseline cognitive performance (BAC-A), current therapy (baseline medications, changes in medication within the study period, lithium (yes/no), antipsychotics (yes/no)) and global daily drug burden, estimated using the WHO defined daily dose (DDD) method [64].

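### Relapse, stopping medication and missed FR sessions all count as dropout, and the default rm-ANOVA would then compare selected completers, with a bias of unknown direction

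*Protocol article*

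**What the plan says.** The protocol article, section 2.7 (Outcome Measures), lists four events that make a patient a dropout. Event (a) is withdrawal of consent. Event (b) is "emergence of a full-blown mood episode and/or major change in drug therapy needed in order to prevent this eventuality within the study period". The list ends with "c) discontinuation of drug therapy for ≥5 consecutive days; (d) missing ≥5 consecutive FR sessions".

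On who can meet rule (d), section 2.5 states: "Participants recruited to the TAU group will not receive FR intervention". The Functional Remediation section gives the schedule: "The program consists of 21 90-minute weekly sessions".

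On analysis, the Statistical Analyses section bases the result on "effect size estimates obtained from within- and between-group differences at repeated measures analyses of variance (rm-ANOVAs". It then adds: "In case of attrition rate > 20%, a mixed model will be employed, under the missing at random (MAR) assumption". The same section says that "participants leaving the study early will be compared with those completing all study procedures".

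On numbers, the sample size section asks for 44 participants and continues: "Assuming 20% attrition, it was decided to set the recruitment target at 54 participants (27 per group". Outcomes are measured at baseline (T0), end of treatment (T1) and six months later (T2) (section 2.6).

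**The concern.** Of the four events, only withdrawal of consent by itself prevents a later FAST assessment. The other three happen after randomisation to patients who could still be assessed.

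Two of them are awkward for a randomised comparison. Rule (d) exists in one arm only. A poorly engaged FR patient can leave the comparison while the equivalent TAU patient stays in it. Rule (b) is itself a bad outcome. It probably worsens FAST, it defines the upper end of the secondary Y-MRS and HAM-D scores, and treatment may influence it.

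If such patients are not assessed or not analysed, the groups compared are no longer the groups randomised. Scores that were never collected cannot be recovered at the analysis stage.

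**Working it through.** **1. The plan's own sample size.** Inputs: f = 0.25, alpha 0.05, 95% power, group × time interaction (sample size section); two groups; three visits (section 2.6). The correlation between visits and the sphericity correction are not stated, so I assumed 0.5 and 1.

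- Noncentrality = f² × N × m / (1 − rho) = 0.0625 × 44 × 3 / 0.5 = 16.5.
- Degrees of freedom: (3 − 1)(2 − 1) = 2 and (44 − 2)(3 − 1) = 84.
- Power = 0.956, so N = 44 is reproduced. With two visits and the same correlation, 54 would be needed.

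The figure of 44 is therefore consistent with an rm-ANOVA on all three visits. Rule (b) runs over the whole study period, so a relapse after T1 could also take an observed T1 score out of a complete-data rm-ANOVA.

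**2. Planned loss against the 20% switch.**

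- Planned loss: 54 − 44 = 10, and 10/54 = 18.5%. The rm-ANOVA stays.
- One more: 11/54 = 20.4%. The mixed model applies.
- The switch is pooled. If all 10 were in FR, that is 10/27 = 37% of the arm, leaving 17 FR against 27 TAU, and the rm-ANOVA would still be used.

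**3. Rule (d).** Missing five sessions in a row leaves 21 − 5 = 16, so a patient who attended 16 of 21 sessions can be a dropout. Suppose FR has no effect, a share p of the FR arm meets the rule, and their FAST is d SD worse than that of the attenders. The full-arm mean is the attenders' mean plus p × d, so dropping these patients shifts the estimate by p × d in favour of FR:

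- 0.10 × 0.5 = 0.05 SD
- 0.15 × 0.8 = 0.12 SD
- 0.20 × 1.0 = 0.20 SD

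If missing sessions is unrelated to outcome, d = 0 and the shift is zero. The document gives neither p nor d; these are assumed ranges.

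**4. Rule (b).** With a FAST gap g between patients who relapse and those who do not, dropping relapsers shifts the difference by (relapse rate in TAU − relapse rate in FR) × g. A positive value is against FR. At equal rates it is zero. If TAU relapses more, a benefit of FR is hidden; if FR increases relapse, harm is hidden.

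**5. The rules together.** This is a simulated completers-only comparison with no true effect and 200,000 patients per arm. The two columns are assumed correlations between liability to drop out and outcome. Values are in SD; negative favours FR.

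| Dropout under (b), TAU / FR | FR dropout under (d) | Correlation 0.3 | Correlation 0.5 |
|---|---|---|---|
| 10% / 10% | 10% | −0.06 | −0.09 |
| 10% / 10% | 20% | −0.10 | −0.15 |
| 20% / 20% | 10% | −0.06 | −0.07 |
| 20% / 20% | 20% | −0.10 | −0.14 |
| 20% / 10% | 0% | +0.04 | +0.08 |
| 20% / 10% | 10% | −0.01 | 0.00 |
| 20% / 10% | 20% | −0.05 | −0.07 |

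At correlation zero, every scenario is within 0.003 SD of zero.

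**The case against.** A reader might infer that the trial is biased toward FR. The document does not support that. Rule (d) favours FR only if patients who miss sessions do worse, which the article does not say. Rule (b) applies to both arms and works against FR if TAU relapses more. The table contains results of either sign and near zero.

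A reader might also infer that the article orders the dropouts' data to be discarded. It does not. Section 2.7 defines who is counted as a dropout and promises to report numbers, patterns, attendance and reasons for non-attendance. The 20% attrition allowance is generic and not tied to the four events. Analysis sets are commonly left to a full protocol or analysis plan, so the lack of an intention-to-treat sentence is not the point here. Exclusion is an inference from the dropout definition, the reference to leaving the study early, and a default method that normally needs complete data.

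Other limits also stand:

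- The rules are narrower than any drug change or any missed session: (b) needs a major change made to avert an episode, and (d) needs five consecutive absences.
- Above 20% attrition a mixed model can use partial data, so the analysis would not be strictly of completers.
- The upper figure of 0.20 SD is stretched. A 20% loss under rule (d) alone is 0.20 × 27 = 5.4 patients, the FR arm's whole attrition allowance.

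None of this removes the one-sided rule, the outcome-related rule, or the choice of rm-ANOVA at the planned level of loss.

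**Conclusion.** The concern holds in a limited form. The stated dropout rules are outcome-related and, for rule (d), confined to one arm. At the planned loss of 18.5% the stated default analysis would most naturally compare selected completers.

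The resulting bias has no known net direction. Rule (d) alone gives 0.05–0.20 SD toward FR for p = 10–20% and d = 0.5–1.0 SD, and zero if attendance is unrelated to outcome. With rule (b) included, the simulated scenarios run from about 0.15 SD toward FR to 0.08 SD against it.

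This rests on two things: the reading that dropouts are not assessed or analysed, and the assumed rates and gaps. Above 20% attrition the mixed model helps only in part. Scores after the event would still be absent, and missing at random would be doubtful after a relapse, though the observed data cannot test it.

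**What to change.** - Separate the events from leaving the study. Record (b), (c) and (d) as intercurrent events with dates, and reserve study exit for withdrawal of consent.
- Assess FAST, BAC-A, MSCEIT, Y-MRS and HAM-D at T1 and T2 in every randomised patient who has not withdrawn consent.
- Make the primary analysis a mixed model of all randomised patients in their assigned arm, whatever the attrition rate, and delete the 20% switch.
- Keep the completer or adherer set as a labelled sensitivity analysis, and add one for departures from missing at random.

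The cost is amendment wording and T1/T2 visits for somewhat fewer than 10 patients, since the planned loss of 10 includes consent withdrawals who cannot be assessed. The estimated effect may be smaller. No clinical rule changes. The wording should be settled before the affected visits fall due.
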